### Assignment of interventions: allocation

#### Sequence generation {16a}

All participants will be randomly divided into the intervention group or the control group in a 1:1 ratio. Randomization will be performed using computer-generated sequence. No stratification is planned in this study.

#### Concealment mechanism {16b}

A computer program will be developed by technicians not related to the study. For each new participant entering the study, the investigator will open the program, and the participant will be assigned randomly. The program is blinded to individuals directly involved in the study.

#### Implementation {16c}

A computer program developed by technicians not involved in the assignment or care of the trial participants will be used to assign participants to intervention or control group. Study investigators will lead participant recruitment, informing participants of all the trial procedures and obtaining their ICF before the initial inclusion in the study. The study investigators will confirm the eligibility of the participant prior to any study procedures being undertaken.

### Assignment of interventions: blinding

#### Who will be blinded {17a}

The participants, clinical doctors, and outcome assessors will remain blinded to the intervention. However, data analysts will not be blinded.

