#### Recruitment {15}

A total of 56 patients will be recruited and participate in the study. Prior to recruitment, investigators will carefully study the medical history, laboratory test, and imaging test of each patient. If the patient meets the inclusion and exclusion criteria, researchers will fully consider the compliance of the patients and informed consent forms (ICFs) will be obtained before collecting any data or performing any intervention. After initial assessment and randomization, patients will receive intervention and 48 h after onset. If the patient still has evidence of organ failure, they will be diagnosed with SAP and will be formally enrolled in the study. The follow-up will be ended when the patients leave the hospital.

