#### Procedure for unblinding if needed {17b}

There should not be any need to unblind the participants. The investigation is not blinded to clinical doctors. Nevertheless, if required, unblinding can be carried out by the study team.

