#### Plans to promote participant retention and complete follow-up {18b}

During study period, participants will stay in hospital. No follow-up after discharge is arranged. If there is a significant protocol violation, data will not be included in the analysis.

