### Statistical methods

#### Statistical methods for primary and secondary outcomes {20a}

Intention-to-treat (ITT): Nno one was excluded from the main analysis set after randomizationPer-protocol set (PPS): good compliance case data that meets the main inclusion and exclusion criteria and reach the primary endpoint

The number of participants selected and complete the study will be listed and the two analysis data sets (ITT and PPS) as specified above will be identified. Cases of protocol violation will also be listed with reasons documented. In terms of outcome indicator analysis, continuous variable indicators will count the number of cases (*n*), mean (*x*), standard deviation (SMD), median (*M*), minimum (min), and maximum (max). The difference between groups will be analyzed using Student’s *t*-test. Counting and grading data will be used to calculate the frequency and composition ratio. The *χ*
^2^ test/chi-square test will be used for differences between groups. Unless otherwise stated, all statistical tests will be conducted in a bilateral manner. All data will be entered in Microsoft Excel, and all statistical analyses will be performed using the SPSS version 25 statistical package.

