#### Methods in analysis to handle protocol non-adherence and any statistical methods to handle missing data {20c}

An ITT data set will be used for protocol non-adherence and no imputation of missing data will be performed for statistical analysis.

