#### Composition of the data monitoring committee, its role and reporting structure {21a}

This is a single-center trial with relatively small sample-size, data monitoring will therefore be conducted by study team. No data monitoring committee is required.

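### Analysts know the arm while exclusion terms are undefined: an avoidable opening for bias in the per-protocol result, and in the primary result if the {18b} exclusion rule is applied

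*Protocol article*

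**What the plan says.** All references are to the Protocol article.

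- **Blinding.** Who will be blinded {17a} covers participants, clinical doctors and outcome assessors, then adds: "However, data analysts will not be blinded".
- **Exclusion.** Plans to promote participant retention and complete follow-up {18b}: "If there is a significant protocol violation, data will not be included in the analysis". What counts as significant, who decides and when are not stated.
- **Per-protocol set.** Statistical methods {20a} defines it as "good compliance case data that meets the main inclusion and exclusion criteria and reach the primary endpoint". No compliance threshold is given, and membership depends partly on the outcome itself.
- **Main set.** The same section defines the ITT set as the main analysis set, with nobody excluded after randomisation. Section {20c} agrees: "An ITT data set will be used for protocol non-adherence and no imputation of missing data will be performed for statistical analysis".
- **Transparency.** Section {20a} also says: "Cases of protocol violation will also be listed with reasons documented". It does not say that the list is closed before allocation is known.
- **Oversight.** Section {17b} says "Nevertheless, if required, unblinding can be carried out by the study team", and {21a} says "No data monitoring committee is required", with data monitoring left to the study team.

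**The concern.** The sentence on analysts is a stated choice, so it cannot be read as detail left to an unseen analysis plan. It is also separate from the conflict between {17a} and {17b} over whether clinical doctors are blinded: settling that conflict either way leaves this sentence standing.

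Unblinded analysts alone do not raise the error rate. The problem is the combination: arm labels are visible, and undefined terms decide whose data are used. With 22 to 28 patients per arm, one or two debatable cases can move a comparison of means noticeably. A reader of the final report could not rule out that knowledge of the arm influenced which cases were dropped.

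**Working it through.** **Inputs.** From Sample size {14}: two-sided 5% level, 90% power, SD 36 h, mean difference 36 h, 22 per arm before dropout, 20% dropout, 56 recruited. From {20a}: Student's t-test, two-sided. Assumed, not in the document: normally distributed times, and the numbers of patients excluded.

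**1. The plan's own figure.** n per arm = 2 × (1.960 + 1.282)² × (36/36)² = 21.01, so 22 per arm and 44 in total. With dropout, 22 / 0.8 = 27.5, so 28 per arm and 56 in total. The stated sizes reproduce.

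**2. Which set is exposed.**

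| Section | Rule | Can a judgement on violation or compliance remove a patient? |
|---|---|---|
| {20a}, ITT | main set, no one excluded after randomisation | No |
| {20c} | ITT used for non-adherence | No |
| {20a}, PPS | good compliance | Yes, from the PPS |
| {18b} | significant violation, not in the analysis | Yes, and the set is not limited to the PPS |

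Section {18b} contradicts the two ITT statements, and the article does not say which governs. If the ITT statements govern, only the PPS result is exposed. If {18b} is applied as written, the primary result is exposed too.

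**3. How far two exclusions move a mean.** Suppose 2 of 22 patients lie 2 SD (72 h) above their arm mean. Removing them lowers that mean by 2 × 72 / 20 = 7.2 h. The standard error of the difference is 36 × √(2/22) = 10.9 h. The shift is therefore 7.2 / 10.9 = 66% of a standard error and 7.2 / 36 = 20% of the planned effect.

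**4. Error rate by simulation with no true effect.** The t-test is two-sided at 5%, and the slowest patients are dropped from the neostigmine arm only:

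| Dropped | 22 per arm | 28 per arm |
|---|---|---|
| 0 | 5.1% | 5.0% |
| 1 | 6.8% | 6.5% |
| 2 | 9.9% | 9.2% |

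A less contrived selection, at 28 per arm: three random patients in each arm are open to being called violators, and whichever subset gives the smallest p-value is dropped. The error is 10.2%.

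**5. The same exclusions without sight of the arm (28 per arm).** Dropping 3 or 6 random patients per arm gives 4.9%. Dropping the 3 or 6 longest times from the pooled data gives 5.2%. Hiding the arm when the decision is made is what removes the inflation.

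**The case against.** The strongest reply is that the main analysis is already protected. Sections {20a} and {20c} keep every randomised patient in the ITT set, so neither undefined term can touch it. This stands, on condition that those sections govern over {18b}. The article does not say that they do.

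Second, no section gives analysts the decision on exclusions. That also stands. A reader might infer that analysts will choose exclusions knowing the arm and that the trial's false-positive rate is therefore inflated. The document does not support this. It leaves the decision-maker unnamed, and it requires violations to be listed with reasons, which gives some transparency.

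Third, the data check in {18a} might be read as another route to exclusion. It is not: someone independent of the project reviews the data and the study team corrects errors. It removes nobody.

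Fourth, the size can be made to look larger by counting only false results in favour of the drug. At 22 per arm these go from 2.6% to 5.4% or 9.1% with one or two drops, so one exclusion appears to double the error. The plan's tests are two-sided, and on that scale one exclusion adds 6.8 − 5.1 = 1.7 points. The selection is also a deliberate worst case that nothing in the document suggests.

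Fifth, analyst discretion is narrow: an unadjusted t-test, with no interim, subgroup or adjusted analysis planned. The analyst's status is openly disclosed, and the timing of the lock on analysis sets is commonly left to an analysis plan. All this lowers the weight of the point. It does not answer it, because the article positively states that analysts are unblinded and gives a conflicting exclusion rule.

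**Conclusion.** The point holds in a limited form. Leaving analysts unblinded while {18b} and the PPS rest on undefined terms creates an avoidable opportunity for exclusions to be influenced by the arm. The exposure is to the PPS result, and to the primary result only so far as {18b} is applied against {20a} and {20c}.

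In the worst case, one or two selective exclusions take the two-sided error from about 5% to 6.8% or 9.9% at 22 per arm, and to 6.5% or 9.2% at 28 per arm. This assumes normal outcomes, no true effect, and deliberate removal of the slowest patients from one arm. It bounds what could happen under those assumptions and is not a forecast. The change is worth making because it costs nothing and lets readers rule the possibility out.

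**What to change.** 1. In {17a}, replace the sentence on analysts with: *Data analysts will work with arms coded A and B; the code, held by the independent technicians or pharmacists, will be released only after the database, the list of protocol violations, ITT and PPS membership and the analysis programs are locked.*
2. Amend {18b} so that a protocol violation affects PPS membership only, in line with {20a} and {20c}. Coding the arms does not by itself remove this contradiction.
3. Define a significant violation and good compliance before the lock, so that PPS membership follows a written rule.

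Cost: a few sentences. The allocation program is already built by technicians unrelated to the study, and injections are prepared by pharmacists outside it, so holders of the code exist. Sample size, visits and treatment are unchanged.

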#### Procedure for unblinding if needed {17b}

There should not be any need to unblind the participants. The investigation is not blinded to clinical doctors. Nevertheless, if required, unblinding can be carried out by the study team.

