### Trial design {8}

This study is a randomized, placebo-controlled, double-blinded, mono-centric, superiority trial. All eligible participants will be randomly divided into intervention group or control group in a 1:1 ratio. Participants will be followed up until they are discharged. The flow chart of this study is shown in Fig. 1.

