#### Relevant concomitant care permitted or prohibited during the trial {11d}

There will be no restrictions regarding concomitant care during the trial.

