### Outcomes {12}

#### Primary outcome

The effect of neostigmine on gastrointestinal motility will be assessed using time span from onset of disease to the first time of spontaneous defection (defined as at least 1 h apart from enema). The defection times will be documented by clinical doctors and reported to study team for documentation.

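### Two consecutive sections say opposite things about whether the clinical doctors, who record the primary outcome, are blinded

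*Protocol article*

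**What the plan says.** All references are to the protocol article.

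- Trial design {8}: "This study is a randomized, placebo-controlled, double-blinded, mono-centric, superiority trial". The Methods paragraph of the abstract also uses the double-blind label.
- Who will be blinded {17a}: "The participants, clinical doctors, and outcome assessors will remain blinded to the intervention". It then adds: "However, data analysts will not be blinded".
- Procedure for unblinding if needed {17b}: "The investigation is not blinded to clinical doctors". The sentence after it reads: "Nevertheless, if required, unblinding can be carried out by the study team".
- Primary outcome, under Outcomes {12}: "The defection times will be documented by clinical doctors and reported to study team for documentation". A defecation counts as spontaneous only if it is at least 1 h away from an enema.
- Relevant concomitant care {11d}: "There will be no restrictions regarding concomitant care during the trial".
- Intervention description {11a}: pharmacists outside the study prepare the active and saline injections, which look the same. Only participants are named there as blinded.

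**The concern.** Who is blinded is a basic design statement, and here it is made twice with opposite content for the same group of people. Staff who follow {17a} would withhold the allocation from treating doctors. Staff who follow {17b} could disclose it and still be acting within the written protocol.

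The group in question is the one through which the primary endpoint reaches the data. The endpoint is the time to a first defecation that qualifies as spontaneous, so it depends on when enemas are given, on when they are recorded, and on when the stool is recorded. With concomitant care unrestricted, a doctor who knows the arm could, without any intent, manage or document the two groups differently. Timing of enteral nutrition is exposed in the same way, since the background section says spontaneous defecation usually serves as the signal to start it. The article does not say in so many words that these doctors order enemas or start feeding. That is a reasonable inference from their role.

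**Working it through.** The contradiction is textual, so the check is to set the statements side by side.

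| Section | Clinical doctors |
|---|---|
| Abstract, Methods; Trial design {8} | Trial is double-blinded, roles not listed |
| Intervention description {11a} | Not mentioned; only participants named |
| Concealment mechanism {16b} | Allocation program hidden from those directly involved in the study |
| Who will be blinded {17a} | Blinded |
| Procedure for unblinding {17b} | Not blinded |

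**Step 1: can the two sections be reconciled?** Both use the same term for the same people, and neither limits its statement to a period or a circumstance. The {17b} sentence describes a standing state. The provision for breaking the code comes separately, in the sentence that follows it. So the sentence cannot be read as describing what happens after an emergency code break.

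**Step 2: does another section decide the matter?** The double-blind label and {16b} lean towards {17a}. {11a} is silent on doctors. A stray negative in {17b} is the likeliest explanation, but the text does not show that.

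**Step 3: does it reach the primary outcome?** Yes. The clinical doctors document the defecation times, and the study team then files what they report.

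**Step 4: does it affect the sample size?** No. From Sample size {14}: SD 36 h, difference 36 h, two-sided 5%, power 90%. Then n per arm = 2 × (1.960 + 1.282)² × 36²/36² = 21.02, rounded up to 22, or 44 in total. Allowing 20% dropout, 22/0.8 = 27.5, rounded up to 28 per arm, or 56. The plan's figures reproduce, and a blinding correction leaves them unchanged.

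**Illustration only.** Suppose there is no true effect but unblinded care or recording shifts the mean difference by b hours. With SD 36 h and 22 per arm, the t-test has 42 degrees of freedom, critical value 2.018 and noncentrality b/(36 × √(2/22)).

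| Assumed shift b | Noncentrality | Two-sided rejection rate |
|---|---|---|
| 0 h | 0 | 5.0% |
| 6 h | 0.553 | 8.4% |
| 9 h | 0.829 | 12.8% |
| 12 h | 1.106 | 19.1% |

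The shifts are assumptions with no source in the documents. The table shows how the test would respond to a bias of a given size. It does not show that such a bias would occur.

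**The case against.** The strongest reply is that {17b} contains a slip of the pen, that everything else points to a double-blind trial, and that the safeguards are real: identical-looking injections from uninvolved pharmacists, a clock-based rule for what counts as spontaneous, and an independent third person who assesses the collected data (section {18a}). These points lower the likely harm. They do not remove the contradiction. The 1 h rule still relies on times that the doctors write down, and a later data check cannot detect care that differed because the arm was known.

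A reader might infer three stronger points, and the documents do not support them.

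- *That code breaking by the study team is a further contradiction.* Section {17b} says that "unblinding can be carried out by the study team", but only if required. Nothing says the team routinely knows the allocation, and {16b} and {17a} point the other way. What remains is that the article does not separate the role that may break the code from the role that measures bowel sounds and judges adverse events. Code-holding detail of that kind may well stand in the full protocol.
- *That unblinded analysts are part of the conflict.* They are disclosed openly in {17a} and nothing contradicts it. How protocol violations ({18b}) and good compliance ({20a}) are judged is a question about analysis sets, separate from blinding.
- *That the false-positive rate would be 8% to 19%.* Those rates follow only from assumed shifts, and only if {17b} governs. They carry no weight for how serious the point is.

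**Conclusion.** The point holds in this form: {17a} and {17b} contradict each other on the clinical doctors, and {17b} also conflicts with the double-blind label. It must be corrected because these doctors record the primary outcome under unrestricted concomitant care, and bias introduced while patients are being treated cannot be repaired at analysis. Confidence in the contradiction is high, since it rests on the wording alone. How much bias would follow if {17b} were applied is unknown. That it could act through care as well as recording assumes that the clinical doctors who document the outcome also direct the patient's care, which the article implies but does not state.

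**What to change.** **Required.** Delete the {17b} sentence on clinical doctors. State one rule, in one place, consistent with {8} and {17a}: participants, clinical doctors and outcome assessors are blinded. Outcome assessors should expressly include the study team members who measure intra-abdominal pressure and bowel sounds or who judge adverse events. Bring {11a} into line, where only participants are named. If patients have already been enrolled, record which rule was followed for them.

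**Cost.** A wording amendment. Blinding the doctors is feasible with what is already planned, because visually identical injections come from pharmacists not involved in the study. The sample size does not change.

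**Optional, low-cost improvements; their absence is not a contradiction.**
- Have any code break done and logged by someone who does not assess outcomes. The article does not say that the pharmacists hold the code or could be reached for this, so the sponsor would have to name the role.
- Settle protocol-violation and per-protocol exclusions before the analysts see the arms.

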### Data collection and management

#### Plans for assessment and collection of outcomes {18a}

Sociodemographic characteristics and required clinical information will be obtained from the hospital information system of PUMCH. IAP and borborygmus of participants will be measured every day by the researcher. A third person with adequate clinical acumen independent to the project will assess the data collected. If inappropriate data is discovered, study team will be notified to remedy the error.

#### Plans to promote participant retention and complete follow-up {18b}

During study period, participants will stay in hospital. No follow-up after discharge is arranged. If there is a significant protocol violation, data will not be included in the analysis.

#### Data management {19}

The data will be collected in a Microsoft Excel database for assessment; data will be kept securely within the organization’s network. All data will be stored with the principal investigator in a password-protected computer for a period of 5 years. All soft copies of the data will be permanently deleted from the computer once the data storage time is over or at the conclusion of the study.

#### Confidentiality {27}

The collected information will remain anonymous; participants will be allocated a participant number for de-identification purposes. The data will be stored in a password-protected computer and will only be accessed by study team.

#### Plans for collection, laboratory evaluation, and storage of biological specimens for genetic or molecular analysis in this trial/future use {33}

Not applicable. No specimens will be collected.

### Statistical methods

#### Statistical methods for primary and secondary outcomes {20a}

Intention-to-treat (ITT): Nno one was excluded from the main analysis set after randomizationPer-protocol set (PPS): good compliance case data that meets the main inclusion and exclusion criteria and reach the primary endpoint

The number of participants selected and complete the study will be listed and the two analysis data sets (ITT and PPS) as specified above will be identified. Cases of protocol violation will also be listed with reasons documented. In terms of outcome indicator analysis, continuous variable indicators will count the number of cases (*n*), mean (*x*), standard deviation (SMD), median (*M*), minimum (min), and maximum (max). The difference between groups will be analyzed using Student’s *t*-test. Counting and grading data will be used to calculate the frequency and composition ratio. The *χ*
^2^ test/chi-square test will be used for differences between groups. Unless otherwise stated, all statistical tests will be conducted in a bilateral manner. All data will be entered in Microsoft Excel, and all statistical analyses will be performed using the SPSS version 25 statistical package.

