## Introduction

### Background and rationale {6a}

Acute pancreatitis (AP) is a seriousthreat to human health globally. It is the third most common gastrointestinal, liver, and pancreatic principal diagnoses from hospital admissions in USA. Over 275,000 patients were admitted because of AP every year, with over 2000 deaths and 2,600,000,000 dollars spent [1–3]. The diagnosis of AP requires 2 of the following features: characteristic abdominal pain, biochemical evidence of pancreatitis, radiographic evidence of pancreatitis. AP can be categorized as mild, moderately severe, or severe based on the revised Atlanta classification [4]. Severe acute pancreatitis (SAP), defined as pancreatitis with persist organ failure (over 48 h), develops in 20–30% of AP patients, with high mortality (15%) [5, 6].

Gastrointestinal dysmotility is a common complication for AP patients, often resulting in abdominal distension, nausea, and vomiting. Delayed feeding and oral feeding intolerance (OFI) may also be associated with gastrointestinal dysmotility. Severe gastrointestinal dysmotility is associated with paralytic ileus and abdominal compartment syndrome (ACS), which can be lethal for SAP patients [7–9]. Currently, there is limited evidence for treating gastrointestinal dysmotility in AP patients.

Early enteral nutrition (EN) plays an important role in the management of AP by protecting the mucosal barrier and reducing bacterial translocation. Delayed feeding (generally defined as over 24 h after onset) is associated with higher rates of infected peripancreatic necrosis, multiple organ failure, and total necrotizing pancreatitis [10–14]. OFI is a well-known complication of AP and the burden can be high. OFI develops in nearly one in six patients with AP, leading to longer length of hospitalization and reduced quality of life [15–19]. ACS, defined by the increased intra-abdominal pressure > 20 mmHg in association with failure of at least one organ system, developed in 12% to 56% of patients and the mortality of SAP patients with ACS is around 24 to 75% [20–24].

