#### Sample size {14}

This is a randomized controlled trial. The bilateral significance level is 5% with an assurance of 90%. We estimate the standard deviation is 36 h, and the mean difference is 36 h. In the case of 1:1 ratio between intervention group and control group, a total of 44 patients will be needed (22 patients in each group). Considering a 20% drop-out rate, 56 patients will be recruited.

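### The t-test, the ITT set that excludes no one and the no-imputation rule cannot all be followed for the primary outcome: patients who die or leave before defecating drop out

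*Protocol article*

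**What the plan says.** All references are to the protocol article.

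- *Primary outcome*: the endpoint is the "time span from onset of disease to the first time of spontaneous defection".
- *Trial design {8}*: "Participants will be followed up until they are discharged". *Provisions for post-trial care {30}* confirms that nothing is observed afterwards.
- *Statistical methods {20a}*: continuous variables are summarised by mean, SD, median and range, and "The difference between groups will be analyzed using Student’s *t*-test". The ITT set is defined as excluding nobody after randomisation. The per-protocol set is "good compliance case data that meets the main inclusion and exclusion criteria and reach the primary endpoint".
- *Methods to handle non-adherence and missing data {20c}*: the ITT set is used, and "no imputation of missing data will be performed for statistical analysis".
- *Sample size {14}*: "We estimate the standard deviation is 36 h, and the mean difference is 36 h", at two-sided 5% and 90% power, giving 44 patients, raised to 56 for 20% drop-out.
- *Background and rationale {6a}*: mortality of severe acute pancreatitis (SAP) is put at 15%. Mortality is also the first item under *Secondary outcome*.

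The t-test is named for continuous variables in general. That it is the primary test follows from the sample size, which is built on a mean difference and an SD, and from the absence of any other method for this outcome.

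**The concern.** The endpoint is a time to an event that some patients may never have while under observation. A patient who dies first, or goes home first, has no value. A t-test cannot use that patient, and the plan forbids filling the gap. The only remaining course is deletion, which the ITT definition rules out.

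The deleted patients are not a random sample. They are the failures on gut motility, and the Introduction itself links severe dysmotility to potentially lethal abdominal compartment syndrome. Reducing mortality is also one of the stated objectives, so the trial's own hypothesis allows the loss to differ between arms. If it does, the arm with more early deaths sheds its slow patients and looks better, while the arm that keeps sick patients alive retains their long times and looks worse.

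**Working it through.** **1. The plan's own figure.** Inputs from *Sample size {14}*: SD 36 h, difference 36 h, two-sided 5%, power 90%.

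n per arm = 2 × (1.960 + 1.282)² × 36² / 36² = 21.0, rounded up to 22, so 44 in total. The exact t-test solution is 22.02 per arm, with power 0.8997 at 22. With drop-out, 22 / 0.8 = 27.5, rounded up to 28 per arm, so 56. The design reproduces as a t-test on means.

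**2. How many could be lost.** 56 × 0.15 = 8.4. This is an upper bound on the expected loss through death, for two reasons. The 15% belongs to SAP, while *Recruitment {15}* and the *Discussion* show that patients are treated before the 48 h criterion is settled, so some never meet it. And a death after defecation loses nothing. The documents give neither the timing of deaths relative to defecation nor any rate of discharge without the event.

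**3. Effect on power.** If all 8.4 were lost, 28 × 0.85 = 23.8 per arm remain and t-test power is 92%. With a further 20% drop-out, 56 × 0.85 × 0.8 = 38 patients remain and power is 85%.

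**4. Effect on the estimate.** Simulation with 28 per arm and log-normal times. The SD of 36 h is the plan's. Assumed are the mean of 120 h, the severity-death correlation of 0.6, the mortality rates, and that all deaths precede defecation unless stated.

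| True effect | Mortality, control / active | t-test on observed times |
|---|---|---|
| 0 h | 15% / 15% | no bias; about 5% rejections |
| 0 h | 10% / 25% | false benefit of about 5 h; 7% to 8% rejections |
| 0 h | 25% / 10% | false harm of about 5 h; about 8% rejections |
| 0 h | 10% / 25%, half of deaths before defecation | 2.9 h; about 6% |
| 0 h | 10% / 25%, one third before | 2.0 h; about 5% |
| 36 h | 15% / 5% | estimate about 32 h; power 92% |

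A second model, with normal times, loss of 5% against 25% and correlations of 0.5 to 0.8, gives shifts of about 5 to 9 h and rejection rates of about 8% to 15%. Against the 36 h design difference, 5 h is 5 / 36 = 14%.

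**5. Power of the alternatives.** True effect 36 h, 28 per arm, equal deaths in both arms, all before defecation.

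| Test | 7.5% deaths per arm | 15% deaths per arm |
|---|---|---|
| t-test, observed times only | about 97% | about 97% |
| Rank-sum, deaths ranked worst | about 94% | 82% to 85% |
| Gray-type test, deaths carried to the end | about 63% | about 47% |

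**The case against.** The strongest reply has four parts.

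*The effect is small and rests on assumptions.* This stands. Unequal mortality, its timing and its correlation with motility are not in the documents, and equal loss produces no bias under the null. A reader might infer that the primary result will be biased, or that about 8 patients will be missing. The documents support neither: the first needs differential loss, for which they give no figure, and the second treats a background rate for SAP as if it were the rate of missing outcomes.

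*Discharge without defecation is likely to be rare.* This is plausible. The Introduction describes spontaneous defecation as usually a signal to start enteral nutrition, and follow-up covers the whole admission. The rule is still needed, but death is the main route of loss.

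*The numbers are already covered.* This also stands. A reader might conclude that the trial is underpowered, but the 20% allowance leaves 92% power even if all 8.4 are lost. The allowance protects size; it does not restore the randomised comparison.

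*A condensed article may leave the handling of death to the analysis plan.* This does not answer the point. The article commits to a t-test, to no imputation and to a set that excludes no one. An analysis plan could repair this only by departing from one of the three.

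**Conclusion.** The concern holds as an inconsistency between stated rules. For any patient without a defecation time, the t-test, the full ITT set and the ban on imputation cannot all be observed. What would be reported as ITT is a comparison restricted to patients who reached the endpoint, and on this point it approaches the per-protocol set.

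The likely size is modest: about 5 h and 7% to 8% false positives under a fairly adverse set of assumptions, less if many deaths follow defecation, and no bias if loss is equal. The direction cannot be known in advance. It affects the only primary endpoint, and *Who will be blinded {17a}* leaves the data analysts unblinded, so a rule chosen after the data are seen would be open to challenge. Severity: should fix.

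**What to change.** In *Statistical methods {20a}* and in the missing-data section {20c}:

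1. State that the primary comparison includes all randomised patients and uses a rank-sum test. Observed times are ranked as they are, patients discharged without the event come after all observed times, and deaths before defecation rank worst.
2. Keep the t-test on observed times as a supportive analysis, labelled as restricted to patients who reached the endpoint.
3. Report deaths before defecation by arm.
4. If wanted, add a competing-risk cumulative incidence as description. The outcome clock starts at disease onset but patients enter at randomisation, so count time from randomisation or handle delayed entry. A reader might think this should be the primary test; at this sample size its power is too low (about 47% to 63% in the scenarios above).

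The change is to wording and analysis only, with no new data. There are two costs. The endpoint becomes a composite of death and motility, so a mortality difference contributes to the result although mortality is also a secondary outcome. And the 90% in *Sample size {14}* must be described as approximate: about 94% at 7.5% deaths per arm, and 82% to 85% at 15%, for a true 36 h effect.
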